## Abstract

**Introduction::**

Hepatocellular carcinoma (HCC) is the most common type of primary liver cancer, and most patients in China are diagnosed at the intermediate or later stages, which is not suitable for the first line therapies. Transarterial chemoembolization (TACE) is a commonly selected therapeutic option for intermediate and later stage HCC in China, but patients often suffer from postembolization syndrome (PES), manifesting as fever, liver area pain, nausea, vomiting, paralyzed intestinal obstruction, and abdominal pain after TACE. We try to conduct a double blinded, randomized, placebo-controlled clinical trial to observe whether Chaihu Guizhi decoction (CGD), a classic traditional Chinese formula, could prophylactically alleviate the incidence of PES in HCC patients after TACE.

**Methods::**

Patients will be randomly assigned sequentially in a 1:1 ratio by using preformed randomization envelopes. After TACE procedures, patients in the treatment group will be administrated with Chinese herbal formula CGD, and patients in the control group with CGD simulations, twice a day, continuously for 7 days. The outcomes are the incidence of PES hospitalization and, complications. SPSS version 22 (IBM, Chicago, IL) will be used for the data, and a *P* < .05 will be considered statistically significant.

**Conclusions::**

The findings will explore the prophylactic effect of CGD in alleviating the incidence of PES following TACE in HCC patients.

**Trial registration::**

OSF Registration number: DOI 10.17605/OSF.IO/FKRSN

## Introduction

1

Hepatocellular carcinoma (HCC) is the most common type of primary liver cancer and it's the third most common cause of cancer-related death worldwide.^[1,2]^ The incidence is highest in China because it's strongly influenced by chronic hepatitis B and C infection.^[3,4]^ The best therapeutic approach for HCC is according to stages, and patients at an earlier stage may benefit from resection, transplantation, or ablation. Unfortunately, most patients in China are diagnosed at the intermediate or later stages, which is not suitable for the first line therapies.

Currently, transarterial chemoembolization (TACE)^[5,6]^ is the most commonly selected therapeutic option for intermediate and later stage HCC in China, and it has become a main clinical application to control the development of HCC to prolong patient's life. However, because of the systemic inflammatory response caused by cytolysis, or necrosis of hepatocytes, with or without the chemotherapy drug toxicity, as many as 60% to 80% of patients^[7,8]^ often suffer from postembolization syndrome (PES), the most common adverse events of TACE, manifesting as fever, liver area pain, nausea, vomiting, paralyzed intestinal obstruction, and abdominal pain, according to many reports.^[7,8]^ Though it is usually considered to be self-limiting, PES could last for 2 weeks.^[9,10]^ In addition, PES was reported to increase the hospitalization, and decreased quality of life in patients.^[11]^

The administration of analgesics, antiemetic, and antipyretics^[11]^ could be applied for PES with certain effects, but how to prevent the occurrence of PES is more important. In China, traditional Chinese herbs are often used for the treatment and prevention of PES following TACE in HCC patients, and they were reported to prevent PES after TACE and prolong overall survival of unresectable HCC patients.^[12]^ However, there is still a lack of high quality evidence to prove the efficacy. Here we try to conduct a double blinded, randomized, placebo-controlled clinical trial to observe whether Chaihu Guizhi decoction (CGD), a classic traditional Chinese formula, could prophylactically alleviate the incidence of PES in HCC patients after TACE.

## Methods

2

### Study design

2.1

This is a prospective, double blinded, randomized, placebo-controlled trial conducted in the Ninth People's Hospital of Chongqing and Chongqing Orthopedic Hospital of Traditional Chinese Medicine from April 1, 2021 to March 31, 2022, (registration number: DOI 10.17605/OSF.IO/FKRSN). The study design is in Fig. 1. The protocol has been approved by the Health Research Ethics Board in the Ninth People's Hospital of Chongqing, and the procedure will be carried out in accordance with the Declaration of Helsinki.

**Figure 1 F1:**
[figure not shown]
Flow diagram of the study.

### Participants

2.2

#### Recruitment

2.2.1

Patients with unresectable HCC and willing to perform TACE in hospital will be assessed for eligibility. Before randomization, all patients will sign a written informed consent, and they can freely choose whether to continue the trial at any time.

#### Inclusion and exclusion criteria

2.2.2

The inclusion criteria are as follows: aged between 18 and 80 years old; with unresectable HCC and willing to perform TACE; Child–Pugh class A disease; serum creatinine level lower than 1.5 mg/dL, and the exclusion criteria are as follows: concurrent underlying cardiac, respiratory, or renal disease; other concurrent primary malignancy, allergic to Chinese herbs.

### Randomization and blinding

2.3

Patients will be randomly assigned sequentially in a 1:1 ratio by using preformed randomization envelopes with SAS software package V.9.4 (Cary, NC). The physicians, patients, data collectors, and outcome assessors will be blinded to the allocation. To maintain blinding, CGD will be provided as granules in the treatment group, and CGD simulation also as granules in the control group.

### Interventions

2.4

#### TACE procedures

2.4.1

TACE procedures will be performed in patients of both group as follows: after percutaneous puncture using Seldinger technique, insert the 5F femoral artery sheath and RH catheter, confirm tumor enhancement, and tumor-feeding arteries with angiography, selectively catheterize arteries, inject Oxaliplatin 100 to 150 mg, followed by embolization with Doxorubicin 20 mg and Lipiodol 20 mL and 1-mm-diameter absorbable gelatin sponge particles.

#### Treatment after TACE

2.4.2

After the TACE, patients in the treatment group will be administrated with Chinese herbal formula CGD, composed of *Ramulus cinnamomi* (Guizhi) 10 g, *Scutellaria baicalensis* (Huangqin) 10 g, *Ginseng* (Renshen) 15 g, *Licorice* (Gancao) 10 g, *Pinellia pinellia* (Banxia) 5 g, *Radix paeoniae alba* (Baishao) 15 g, *Jujube* (Zao) 10 g, *Ginger* (Shengjiang) 10 g, and *Radix bupleuri* (Chaihu) 30 g. The herbs will be provided as concentrate-granules in one package and quality controlled by Beijing Tcmages Pharmaceutical CO., Ltd. Patients will orally take 100 mL of the CGD decoction twice a day, continuously for 7 days.

Patients in the control group will be administrated with CGD simulations twice a day, continuously for 7 days. The simulations are composed of amylum, which is the same with CGD granules in appearance, taste, dosage, and administration methods. If PES in both groups cannot be alleviated after taking CGD or CGD-simulations, patients will be treated with antiemetic for nausea and vomiting, analgesics for pain, and antipyretics for fever.

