### Outcome measures

2.5

The primary outcome is the incidence of PES manifesting as one or several of the following symptoms: nausea, vomiting, fever, paralyzed intestinal obstruction, and abdominal pain at 1d, 3d, 7d, and 14d. The secondary outcomes are length of hospitalization after the treatment, and the incidence of complications at d 14. All related complications and adverse events (AEs) will also be recorded.

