### Sample size

2.6

It was previously reported that the incidence of PES is approximately 70%,^[13]^ and our preliminary study showed that the incidence was 30% after taking CGD. Therefore, the sample size will be 25 in each group, taking a 2-sided *t* test with α = 5% and 1–β = 80%, and a potential dropout of 10%.

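### Starch as the only stated placebo ingredient does not support the claimed match in appearance and taste, so patient blinding of the symptom-based primary outcome is in doubt

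*Protocol article*

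**What the plan says.** Section 2.4.2 (Treatment after TACE) gives the placebo's composition and its likeness to the active product in one sentence: "The simulations are composed of amylum, which is the same with CGD granules in appearance, taste, dosage, and administration methods". It names no colourant, bittering agent, flavouring or low-dose herb.

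The same section lists nine herbs for CGD, among them cinnamon twig, ginger, licorice and bupleurum. It describes the supply, "The herbs will be provided as concentrate-granules in one package", and the use: "Patients will orally take 100 mL of the CGD decoction twice a day, continuously for 7 days".

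Section 2.3 (Randomization and blinding) states that "The physicians, patients, data collectors, and outcome assessors will be blinded to the allocation". The means it gives is the dosage form: "To maintain blinding, CGD will be provided as granules in the treatment group, and CGD simulation also as granules in the control group".

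Section 2.5 (Outcome measures) counts a patient as having PES on "one or several of the following symptoms: nausea, vomiting, fever, paralyzed intestinal obstruction, and abdominal pain".

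**The concern.** The article does not leave the placebo's make-up to another document. It states what the placebo is made of, and it states a property that starch by itself would not be expected to have. A starch granule dissolved in water lacks the colour, smell and bitterness of a nine-herb concentrate. A placebo made exactly as written would put patient blinding at risk.

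This matters because of how the primary outcome is built. One symptom is enough for a case, and two of the five, nausea and abdominal pain, are known only because the patient reports them. A blinded assessor does not protect those two if the patient has guessed the arm. If such reporting differed between arms, a difference in PES incidence could not be credited to the herbs with confidence. Lost blinding cannot be restored at analysis, so the point has to be settled before the first dose.

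**Working it through.** **1. The two products side by side (section 2.4.2).**

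| | CGD | Placebo |
|---|---|---|
| Stated content | Nine herbs: 10 + 10 + 15 + 10 + 5 + 15 + 10 + 10 + 30 = 115 g | Amylum; nothing else named |
| Form | Concentrate granules | Granules (section 2.3) |
| Intake | 100 mL, twice daily for 7 days: 2 × 7 = 14 drinks | Twice daily for 7 days; administration said to be the same |
| Appearance and taste | Those of the herbal concentrate | Declared the same as CGD |

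Nothing in the placebo column produces the last row. Section 2.3 adds only that both arms receive granules. That matches the form in which the product is supplied, not the drink that the patient tastes up to 14 times.

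**2. Which parts of the outcome are exposed (section 2.5).** Nausea and abdominal pain are patient-reported. Fever, vomiting and paralysed intestinal obstruction can be measured or observed. Expectation can change a patient's PES status mainly where nausea or pain is the only component present. The article does not say how often that would be.

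**3. The plan's own figure.** The blinding statement contains no number, but the illustration below uses the planned size, so that was checked first. Inputs from section 2.6 are 70% v 30%, two-sided 5%, 80% power, a t test and 10% dropout. With SD = √(0.70 × 0.30) = √0.21 = 0.458, the standardised difference is 0.40/0.458 = 0.873. The two-sample t test then needs 21.6, so 22 per group, and 22/0.90 = 24.4, so 25. The stated 25 per group reproduces and is not disputed.

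**4. Illustration of what a reporting gap could do.** Assume no true effect, with incidence around the 70% of section 2.6. Let differential reporting move the recorded rates to p₁ (placebo) and p₂ (CGD). The rejection rate is the sum, over all pairs (x, y) with two-sided P < .05, of Bin(x; n, p₁) × Bin(y; n, p₂). Section 2.7 allows either a chi-squared or a Fisher exact test, so both are shown (chi-squared uncorrected).

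| Recorded rates, placebo v CGD | Gap | n = 25: Fisher | n = 25: chi-squared | n = 22: Fisher | n = 22: chi-squared |
|---|---|---|---|---|---|
| 70% v 70% | 0 | 2.3% | 5.4% | 2.4% | 4.8% |
| 75% v 65% | 10 points | 6.6% | 12.6% | 6.2% | 10.7% |
| 70% v 60% | 10 points | 7.0% | 12.5% | 5.7% | 10.0% |
| 80% v 60% | 20 points | 23.1% | 35.2% | 20.6% | 29.8% |
| 70% v 50% | 20 points | 23.2% | 33.4% | 17.5% | 26.4% |

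At 25 per arm, a 10-point gap gives about 7% to 13% and a 20-point gap about 23% to 35%. No figure in the article supports any particular gap. The calculation also shifts the whole composite, although only part of it is patient-reported.

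**The case against.** A reader might infer that patients *will* know their arm and that the trial is in effect open-label. The article does not support that. It asserts a match in appearance, taste, dosage and administration, and states that patients and assessors are blinded. It says the placebo is composed of amylum, not of amylum only, and an article may leave an excipient list to the full protocol. Each patient receives one product and never compares the two, so a difference that is obvious side by side need not be noticed. These points stand, and they limit the conclusion to patients *may* be able to tell. They do not remove the defect. The article chose to state composition and match together, and if other excipients exist the sentence needs correcting. A bland drink presented as a herbal decoction can also be recognised without a comparator.

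A reader might also infer that any bias must favour CGD. That is not shown. Section 2.4.2 provides antiemetics, analgesics and antipyretics when PES is not relieved. Earlier rescue among placebo patients could lower their later recorded symptoms and pull against CGD. The direction of any dropout bias is equally unknown.

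Finally, three of the five components are observable, the assumed gaps are not taken from the article, and chi-squared is the more liberal of the two permitted tests. With Fisher's test a 10-point gap barely lifts the error rate above the nominal 5%. All of this stands, and the figures should be read only as illustration.

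**Conclusion.** The point holds in limited form. As stated, the placebo's composition does not support its claimed likeness to CGD, and the shared granule form does not make up the difference. Patient blinding is therefore doubtful rather than shown to fail. The exposure falls mainly on nausea and abdominal pain, either of which can make a case alone; fever, vomiting and obstruction are less exposed. The size and net direction of any bias cannot be derived from the article. The false-positive rates above depend on an assumed gap applied to the whole composite, in the direction favouring CGD, with no true effect and incidence near 70%. The point should be corrected before dosing begins, but it does not by itself invalidate the design.

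**What to change.** In section 2.4.2, replace amylum as the sole stated ingredient with starch plus colourant, bittering and aroma excipients. Match these to CGD both as granules and as the 100 mL drink, and state that the match is checked before release. If such excipients are already planned, name them. If a match cannot be achieved, delete the claim of identical appearance and taste and do not describe patients as blinded in section 2.3 or elsewhere.

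In section 2.5, keep the composite but add separate reporting by arm of the observable components (fever, vomiting, intestinal obstruction) and of nausea and abdominal pain. A reader can then see whether any difference rests on patient report alone.

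A question at day 7 asking patients to guess their arm is optional.

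The cost should be a modest reformulation for about 25 placebo patients and a little extra tabulation. The article names a company for the herbs but not for the placebo, so the reformulation cost cannot be confirmed from it. The sample size does not change.

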### Outcome measures

2.5

The primary outcome is the incidence of PES manifesting as one or several of the following symptoms: nausea, vomiting, fever, paralyzed intestinal obstruction, and abdominal pain at 1d, 3d, 7d, and 14d. The secondary outcomes are length of hospitalization after the treatment, and the incidence of complications at d 14. All related complications and adverse events (AEs) will also be recorded.

### Sample size

2.6

It was previously reported that the incidence of PES is approximately 70%,^[13]^ and our preliminary study showed that the incidence was 30% after taking CGD. Therefore, the sample size will be 25 in each group, taking a 2-sided *t* test with α = 5% and 1–β = 80%, and a potential dropout of 10%.

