### Statistical methods

2.7

Continuous data will be expressed as mean ± standard deviation, and categorical data as percentages (%). The difference of continuous data will be analyzed by Student *t* test, Wilcoxon rank-sum test, or Manne–Whitney *U* test, and Chi-squared test or Fisher exact test for categorical data. SPSS version 22 (IBM, Chicago, IL) will be used for the data, and a *P* < .05 will be considered statistically significant.

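### Section 2.6 sizes a yes/no primary outcome with a t test; after dropout, power is about 77–81% by uncorrected chi-squared but only about 67–75% by Fisher exact

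*Protocol article*

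**What the plan says.** Section 2.5 makes the primary outcome the incidence of PES, so each patient either has it or does not. Section 2.6 takes from an earlier report that "the incidence of PES is approximately 70" per cent, and adds that "our preliminary study showed that the incidence was 30% after taking CGD". From these it concludes that "the sample size will be 25 in each group, taking a 2-sided *t* test with α = 5% and 1–β = 80" per cent, with "a potential dropout of 10" per cent. Allocation is 1:1 (section 2.3). Section 2.7 keeps the Student t test for continuous data and gives "Chi-squared test or Fisher exact test for categorical data".

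**The concern.** Sections 2.6 and 2.7 do not match. The size comes from a test for means, while the outcome is a proportion that section 2.7 will compare with a different test. Section 2.6 also gives no standard deviation, which a t test calculation needs. This is the only power statement for the primary outcome of a 50-patient trial. If the 80% depends on a test the trial will not use, readers cannot tell what chance the trial has of detecting the planned difference.

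**Working it through.** **Inputs.** From section 2.6: control rate 0.70, CGD rate 0.30, two-sided α 0.05, power 0.80, dropout 10%, 25 per group. From section 2.3: 1:1 allocation. Assumed, because the article gives none: SD = √(0.7 × 0.3) = √0.21 = 0.458.

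**1. Reproducing the stated 25.** Two-sample t test on the 0/1 outcome, difference 0.40, standardised difference 0.40/0.458 = 0.873. The noncentral t calculation gives n = 21.6, so 22 evaluable per group (nominal power 80.7%). Then 22/0.9 = 24.4, rounded up to 25. This matches the article exactly.

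**2. Two-proportion formulas** (z values 1.960 and 0.842, mean rate 0.5):

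- Pooled variance: n = [1.960 × √(2 × 0.5 × 0.5) + 0.842 × √(0.21 + 0.21)]² / 0.40² = (1.386 + 0.545)² / 0.16 = 23.3, so 24 evaluable; 24/0.9 = 26.7, so 27 randomised.
- Unpooled variance: n = (1.960 + 0.842)² × 0.42 / 0.16 = 20.6, so 21 evaluable; 21/0.9 = 23.3, so 24 randomised.
- With continuity correction, which approximates Fisher exact: 28.1, so 29 evaluable; 29/0.9 = 32.2, so 33 randomised.

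The stated 25 lies between the unpooled and pooled answers (24 and 27) and well below the continuity-corrected one (33).

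**3. Exact power at 70% v 30%.** All pairs of binomial counts are enumerated, and the probabilities of tables with P < .05 are summed. Dropout of 10% from 50 leaves 45 patients, or 22.5 per group, so the relevant splits are 22/22, 22/23 and 23/23.

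| Analysed per group | Uncorrected chi-squared | Fisher exact |
|---|---|---|
| 22/22 | 77.8% | 67.3% |
| 22/23 | 76.9% | 74.7% |
| 23/23 | 80.9% | 71.3% |
| 25/25 (no dropout) | 85.9% | 78.2% |

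Against 80%, chi-squared falls short by 2.2 points at 22/22 and 3.1 at 22/23, and not at all at 23/23. Fisher exact falls short by 12.7, 5.3 and 8.7 points at the same splits, and by 1.8 points with no dropout. The smallest equal group size at which Fisher exact reaches 80% is 29 (81.4%; 28 gives 79.0%).

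**4. Type I error of uncorrected chi-squared at 25/25.** By the same enumeration with equal rates in both groups, it is 6.5% at a common rate of 50% and 5.4% at 30% or 70%. Part of the 85.9% is therefore bought with an error rate above the stated 5%.

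**The case against.** The strongest reply is that the number is nearly right even though the label is wrong. Under uncorrected chi-squared, power straddles 80%. The unpooled two-proportion formula asks for only 24 randomised per group, which 25 covers, and the pooled formula asks for two more per group. Exact power does not rise smoothly with n either: chi-squared gives 84.0% at 27/27, less than at 25/25. All of this stands, so a reader who infers that the trial is underpowered whichever test is used goes further than the figures allow.

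A second tempting inference is that naming two tests leaves the verdict to be chosen after the data are seen. At 22/22, a result of 15/22 v 8/22 gives P = .035 by chi-squared and P = .069 by Fisher exact, and under the planning rates the two tests disagree in 10.6% of trials. At 22/23, the split that 45 evaluable patients implies, they disagree in only 2.2%. More importantly, section 2.7 is a one-line summary for all categorical data, and a journal article commonly leaves the rule for choosing to the analysis plan, which is not shown. If that rule were the usual one based on small expected counts (an assumption), planning rates give about 11 per cell and chi-squared would apply. The open choice is therefore not an error in itself. It matters here only because the stated 80% depends on which test is used.

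The reply does not explain why section 2.6 relies on a t test for a binary outcome, nor does it rescue the 80% under Fisher exact.

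**Conclusion.** The point holds in a limited form. The test named in section 2.6 does not fit the outcome and is not the one section 2.7 assigns to it. After the planned dropout, power is about 77–81% by uncorrected chi-squared, a shortfall of 0 to 3 points, and about 67–75% by Fisher exact, a shortfall of about 5 to 13 points. Fisher exact misses 80% even with no dropout.

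These figures assume the planning rates of 70% and 30%, one binary PES status per patient, and dropout spread about evenly between the groups. That a t test with SD 0.458 produced the 25 is an inference from the exact match, since the article gives no SD; the power figures do not depend on it. This should be fixed, but it is not a flaw that must be cured before the trial can be interpreted.

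**What to change.** In section 2.6, replace the t test with the two-proportion test that will be used for the primary outcome. For 25 randomised per group less 10% dropout, restate the power as about 77–81% if that test is the uncorrected chi-squared, or about 67–75% if it is Fisher exact.

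If the sponsor prefers to quote about 86% for all 25 per group by chi-squared, the text should say that this needs a usable PES outcome for every patient who drops out, and that the exact type I error can reach about 6.5%.

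The cost is a change of wording and a slightly less favourable stated power. No extra patients are needed.

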### Statistical methods

2.7

Continuous data will be expressed as mean ± standard deviation, and categorical data as percentages (%). The difference of continuous data will be analyzed by Student *t* test, Wilcoxon rank-sum test, or Manne–Whitney *U* test, and Chi-squared test or Fisher exact test for categorical data. SPSS version 22 (IBM, Chicago, IL) will be used for the data, and a *P* < .05 will be considered statistically significant.

